# Ruxolitinib in GvHD (RIG) study: a multicenter, randomized phase 2 trial to determine the response rate of Ruxolitinib and best available treatment (BAT) versus BAT in steroid-refractory acute graft-versus-host disease (aGvHD) (NCT02396628)

**DOI:** 10.1186/s12885-018-5045-7

**Published:** 2018-11-19

**Keywords:** Steroid-refractory GvHD, Ruxolitinib, JAK inhibitor, Biomarkers, Inflammatory cytokines

## Abstract

**Background:**

Graft-versus-Host Disease (GvHD) causes significant morbidity and mortality in patients after allogeneic stem cell transplantation. Donor T-cells cause inflammation and tissue damage in GvHD target organs such as liver, gut and skin. Cytokine receptor associated kinases JAK1 and JAK2 are critical for inflammatory cytokine response in GvHD. Ruxolitinib is a small molecule inhibitor of JAK1 and JAK2. Preliminary data indicated substantial clinical activity in patients with steroid-refractory (SR) acute and chronic GvHD.

**Methods:**

The RIG-study is an investigator-initiated open-label, multicenter, prospective randomized controlled two-arm phase 2 study, comparing the efficacy of ruxolitinib and best available treatment (BAT) versus BAT in steroid-refractory acute GvHD (SR-aGvHD). Patients with acute skin, intestinal or liver GvHD > grade 1 and failure of previous treatment are eligible. The trial aims to include 160 patients who will be randomized in a 1:1 ratio and stratified by GvHD grade (≤ grade 3 versus grade 4) and number of previous immunosuppressive treatments (≤ 3 versus ≥4). The primary endpoint is the overall response rate at day 28, defined as: Improvement of at least one stage in the severity of acute GvHD in one organ without deterioration in any other organ, or disappearance of any GvHD signs from all organs without requirement for new systemic immunosuppressive treatment. Secondary objectives include time to response, overall survival, event-free survival, non-relapse mortality (NRM), failure-free survival, graft failure rates, quality of life and changes in serum levels of pro-inflammatory cytokines and GvHD-related biomarkers.

**Discussion:**

This randomized prospective trial will provide further evidence if the retrospectively collected data demonstrating activity of ruxolitinib for SR-aGvHD can be reproduced. A major advantage of ruxolitinib might be the limited and predictable toxicity profile compared to other immunosuppressive therapies that mainly includes viral reactivation and cytopenias. This trial will establish candidate biomarkers to predict and monitor responses to ruxolitinib. As a next step ruxolitinib might be tested upfront against steroids or in a preemptive manner to prevent GvHD to occur.

**Trial registration:**

NCT02396628 (registration date 17.07.2015); DRKS00007939 (registration date 26.03.2015).

**Electronic supplementary material:**

The online version of this article (10.1186/s12885-018-5045-7) contains supplementary material, which is available to authorized users.

## Background

Steroid-refractory GvHD constitutes the major factor for morbidity and accounts for up to one third of deaths in patients after allogeneic stem cell transplantation [1]. For these patients, there is currently no established standard treatment. Available treatments such as mycophenolate mofetil (MMF), etanercept, daclizumab, basiliximab or Anti-T lymphocyte globulin (ATG) display limited clinical activity with response rates of 20–40% [2]. The anti-CD52 antibody alemtuzumab has been reported to induce high response rates (70%) in patients with aGvHD but however, high rates of infectious complications such as CMV reactivation, bacterial infection, and invasive aspergillosis preclude the broad application of alemtuzumab in steroid refractory GvHD [3–5]. Thus there is a high medical need for novel, active treatments in patients with SR-aGVHD.

The pathophysiological hallmark of GvHD after allogeneic hematopoietic stem cell transplantation (allo-HCT) is an allogeneic donor T cell response against recipient antigens. This process is aggravated by increased processing and presentation of host antigens by donor antigen presenting cells (APCs) following conditioning treatment [6–8]. The allogeneic T cell response leads to inflammation, tissue damage and fibrosis and is mediated by extensive production of inflammatory cytokines such as IL-1, IL-2R, IL-6 and TNF [2]. The signal transmission of inflammatory cytokines in effector cells requires activation of specialized kinases from the family of the Janus kinases. These kinases, JAK1, 2 and 3 are linked to cytokine receptors, and are activated upon binding of the cytokine to the receptor of the inflammatory effector [6, 7]. The development of GvHD in humans is preceded by a dramatic change in the intestinal microflora [2, 9], which could be in part due to a massive influx of neutrophils into the intestinal immune compartment [10] because neutrophils can release proteases and antimicrobial peptides [11] that affect bacteria. This neutrophil infiltration was also observed at late time points after allo-HCT in patients with active GvHD [12]. It was shown that neutrophil activation is dependent on JAK 1/2 signaling [13, 14].

The JAK1/2 kinase inhibitor ruxolitinib (INC424) was approved for intermediate or high-risk myelofibrosis in 2011 and for polycythemia vera with an inadequate response to or intolerance to hydroxyurea in 2014. In myelofibrosis, ruxolitinib lead to sustained clinical remissions with regard to constitutional symptoms, weight loss and spleen size in the majority of treated patients [15]. Of note, clinical responses correlated with a marked reduction in inflammatory plasma cytokines [16]. Importantly, cytokines down-regulated by ruxolitinib in patients with myelofibrosis correspond to inflammatory effectors that mediate tissue damage and inflammation in GvHD. These are mainly the cytokines IL-1, IL-6, TNF and IFN-γ [8, 16].

### Rationale for the trial

Since ruxolitinib suppresses the JAK1/2 dependent cytokine response, we hypothesized that ruxolitinib might attenuate the cytokine mediated inflammatory tissue damage in GvHD and thus might favorably affect the severity and course of GvHD after allo-HCT. In vitro, in an allogeneic system (major mismatch mixed-lymphocyte reactions) we demonstrated that co-incubation with ruxolitinib strongly suppressed both the proliferation of allogeneic T cells and the production of inflammatory cytokines [17]. Using a very aggressive major mismatch mouse model of aGvHD (C57BL/6 on BALBc) ruxolitinib treatment significantly prolonged survival of animals [17]. In addition, in these animals a reduced weight loss was shown, significantly reduced histopathological GvHD severity, suppression of inflammatory cytokines in the serum and a reduction of donor T cells in GvHD target organs such as the intestines. Moreover, we observed that ruxolitinib led to increased frequencies of FoxP3+ regulatory T cells. This cell type was previously shown to lead to long-lasting tolerance [18] as compared to the short-term immunosuppression achieved by conventional medication for GvHD.

Because of this strong evidence of activity of ruxolitinib in animal models, we treated six patients with acute and chronic GvHD with ruxolitinib in a pilot trial [17]. All patients responded with respect to clinical GvHD symptoms and serum levels of pro-inflammatory cytokines. To extend these preliminary findings, we have collected data from a total of 19 stem cell transplant centers in Europe and United States. In this analysis we reported outcome data from 95 patients who received ruxolitinib for corticosteroid-refractory GvHD (skin, mucosa, intestine, liver, lung, musculoskeletal) between 01/2012 and 04/2015 [19]. Patients were classified as having acute (*n* = 54) or chronic (*n* = 41) GvHD. The median number of previous GvHD-therapies was 3 for aGvHD (range: 1–7) and 3 for chronic GvHD (range: 1–10). The overall response rate was 81.4% (44/54) in aGvHD comprising 25 CRs (46%). In cGvHD the overall response rate was 85% (35/41). Clinical improvement was at a median time to response of 1.5 (1–10) weeks and 3 (1–25) weeks after initiation of ruxolitinib treatment in acute and chronic GvHD, respectively. GvHD relapsed in 6.8% (3/44) and 5.7% (2/35) of the ruxolitinib-responsive patients with acute or chronic GvHD. In this analysis, the median follow-up was 22 (3–98) and 25 (2–112) weeks for acute or chronic GvHD patients, respectively. Cytopenias (anemia, leukopenia or thrombocytopenia) and Cytomegalovirus (CMV) reactivation were the most frequently observed adverse events during the time of ruxolitinib treatment occurring in both acute (30/54, 55.5% and 18/54, 33.3%) or chronic (7/41, 17% and 6/41, 14.6%) GvHD patients [19]. Cytopenias had preceded ruxolitinib treatment in 51.8% (28/54) and 14.6% (6/41) of the patients with acute or chronic GvHD. Relapse of the underlying malignancy occurred in 9.2% (5/54) and 2.4% (1/41) of the patients with acute or chronic GvHD, respectively. With a median follow up of 19 months (aGvHD) and 24 months (cGvHD), the 1-year overall survival (OS) was 62.4% for SR-aGvHD (CI: 49.4–75.4%) and 92.7% SR-cGvHD (CI: 84.7–100%) [20]. The estimated median OS was 18 months for aGvHD and not reached for cGvHD patients. The median duration of ruxolitinib treatment was 5 and 10 months for patients with SR-aGvHD and SR-cGvHD, reflecting the different biology of the diseases. 22/54 (41%) SR-aGvHD patients and 10/41 (24%) SR-cGvHD patients had an ongoing response, were free of any immunosuppression and free of ruxolitinib. In responders, GvHD-relapse or GvHD-progression was observed in 14/45 (31%) and 13/36 (36%) patients with SR-aGvHD and SR-cGvHD. Responses to re-treatment with ruxolitinib or any immunosupressive therapy was seen in 11/14 (78%) and 11/13 (86%) patients with SR-aGvHD and SR-cGvHD, respectively. These findings indicated that patients with SR-aGvHD and SR-cGvHD may benefit long-term from ruxolitinib treatment with an OS that is relatively high for steroid-refractory GvHD.

In addition to these data, a prospective clinical trial testing the effects of the JAK1 specific inhibitor itacitinib (INCB039110) in patients with steroid refractory aGvHD indicated an acceptable safety profile [21]. This trial tested the effect of 2 different doses (200 mg and 300 mg PO daily). The reported preliminary ORRs were 83% for first-line therapy patients and 64% for steroid refractory patients.

### Design

Our retrospective analysis demonstrated that ruxolitinib was active and could be safely administered in patients with steroid-refractory GvHD. Based on these data, this study will prospectively evaluate whether ruxolitinib as add-on to BAT is superior to BAT alone in SR-aGvHD. BAT follows current recommendations of the Onkopedia/DGHO guidelines for treatment of aGvHD [22].

The RIG-study is an open-label, multicenter, randomized two-arm phase II study in which patients are randomized to ruxolitinib and BAT versus BAT (Fig. 1). It is planned to randomize 160 patients for the study. Internet-based randomization to one of the two treatment groups is performed in a 1:1 ratio stratified by aGvHD grade (≤ grade 3 versus grade 4) and number of previous immunosuppressive treatments (≤ 3 versus ≥4). Patients will be recruited in 11 transplantation centers in Germany located in Berlin, Bonn, Cologne, Dresden, Freiburg, Hamburg-Eppendorf, Heidelberg, Homburg, Marburg, Munich, and Würzburg. All participating centers are highly experienced in the treatment of patients with aGvHD and stem cell transplantation.

**Fig. 1 Fig1:**
[figure not shown]
Trial diagram of the RIG-study

### Study objectives and endpoints

#### Primary endpoint

The primary objective of this trial is to evaluate the efficacy of ruxolitinib added to BAT as compared to BAT alone at day 28 after randomization. The primary endpoint is the overall response rate (ORR) at day 28 defined as proportion of patients in each arm demonstrating partial (PR) or complete response (CR) without requirement for additional systemic immunosuppressive therapy (IST) at day 28 after randomization. PR and CR are defined as improvement of at least one stage in the severity of aGvHD in one organ without deterioration in any other organ (PR) or disappearance of any GvHD signs from all organs (CR) without requirement for addition of new IST, as compared to time of randomization.

#### Secondary endpoints

ORR at day 14Proportion of patients in each arm who achieve a PR or CR without requirement for additional systemic IST, persisting for at least 4 consecutive weeks within 8 weeks after randomization.Time to response, defined as time from randomization to the date of first documentation PR or CR. Death or relapse/progression of underlying hematologic disease without prior response will be considered to be a competing event. Comparison of treatment arms is conducted until day 28 only, as crossover to ruxolitinib is offered to non-responders then.Rate of patients with treatment failure until day 28 after randomization.Duration of response, assessed for responders only by calculating the time from first response to the date of first observation of aGvHD relapse/progression or the date of additional IST for GvHD. Onset of chronic GvHD (cGvHD) or death without prior observation of aGvHD relapse or progression is considered to be a competing events, and observations where neither occurred are treated as censored observations.Overall survival (OS) defined as time from randomization to the date of death from any cause.Event-free survival (EFS) defined as the time from randomization to the date of recurrence of underlying hematologic disease, graft failure or death due to any causeNRM defined as the time from randomization to the date of death not preceded by hematologic disease recurrence. Hematologic disease recurrence / progression are considered to be a competing event.Failure-free survival (FFS) is defined as the time from randomization to recurrence of underlying hematologic disease, graft failure, NRM or addition of new systemic IST for GvHD. Onset of cGvHD is considered as a competing event.Rate of patients in whom failure to taper steroids below methylprednisolone dose of 0.5 mg/kg/day (or equivalent < 0.6 mg/kg/day of prednisone /prednisolone) was observed within 56 days after randomization OR addition of any new IST for GvHD due to failure to taper steroids below methylprednisolone dose of 0.5 mg/kg/day (or equivalent < 0.6 mg/kg/day of prednisone/prednisolone)Rate of patients discontinued ruxolitinib treatment for at least 4 weeks.Discontinuation rate of steroid therapy for at least 4 weeks.ORR at day 14 in this group, defined as proportion of patients demonstrating PR or CR without requirement for additional systemic IST at day 14 after date of cross over from BAT alone to ruxolitinib/BAT.ORR at day 28 in this group, defined as proportion of patients demonstrating PR or CR without requirement for additional systemic IST at day 28 after date of cross over from BAT alone to ruxolitinib/BAT.Proportion of patients who achieve a PR or CR without requirement for additional systemic IST, persisting for at least 4 consecutive weeks within 8 weeks after the date of cross over from BAT only to ruxolitinib/BAT.Cumulative steroid dose until day 56.Reduction of GvHD blood biomarkers on day 8 randomization.Relapse rate of underlying hematologic disease, calculated as incidence rate, time from randomization to the date of relapse diagnosis. Death without prior relapse will be considered as a competing event.Graft failure incidence rates, calculated as time from randomization to the date of graft failure diagnosis. Death without prior graft failure will be considered as a competing event.Quality of life (QoL): EORTC QLQ-C30 and EORTC QLQ-C29.Time from randomization to the start date of any cGvHD. Hematologic relapse/progression and death without prior cGvHD will be considered as competing events.Type, frequency, severity and relationship of adverse events to investigational product, engraftment, infections.Frequency of CMV reactivation.Number of nights in hospital.

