#### Statistical planning

The sample size calculation is based on the primary endpoint response (ORR). An expected proportion of 30% for the patients with best available treatment and an expected alternative proportion of 50% for the patients with acute GvHD treated with ruxolitinib is assumed. As there is currently no satisfactory active treatment available for patients with steroid-refractory GvHD, the alternative assumption is based on published data of 60 patients with acute and chronic GvHD treated with ruxolitinib [17, 19] and on recent papers for BAT [3–5]. The study is planned to detect a response difference between treatment arms at a one-sided significance level α = 5% with a power of 1-β = 80%, when the response probabilities are 50% (ruxolitinib) and 30% (BAT). Based on the χ2 Test, 148 patients (74 per group) need to be included in the analysis. A small number of drop-outs not evaluable for the intention-to-treat analysis of the primary endpoint may occur. Further missing response will be evaluated as non-response according to the intention-to-treat principle. This might blur the assumed difference between treatment groups. Therefore we increased the calculated sample size by 8%, and 160 patients will be randomized.

The primary analysis will be based on the full analysis set (FAS) and will be conducted with a logistic regression model of the primary endpoint response to GvHD treatment as defined above. The model will include treatment assignment (ruxolitinib and BAT vs BAT only) and the stratification variables aGvHD grade (≤ grade 3 versus grade 4) and number of previous immunosuppressive treatments (≤ 3 versus ≥4) as covariates, and the primary hypothesis will be tested at a one sided level α = 5% within this model. Odds ratios will be calculated with two-sided 90% confidence intervals (CI), and the null hypothesis will be rejected in favour of the alternative, if the lower bound of the CI for the odds ratio of ruxolitinib and BAT compared to BAT only is above 1. Patients with missing response evaluation will be counted as non-responders. This analysis will be repeated in the per protocol (PP) population as a sensitivity analysis. Additionally, two-sided 95% CI will be reported in order to provide comparability with data from literature.

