Binary secondary endpoints (e.g. proportion of patients with CR, proportion of patients dis-continuing treatment) will be estimated as rates and presented with exact two-sided 95% confidence intervals derived from the binomial distribution. Furthermore, the same type of logistic model using treatment assignment, aGvHD grade and number of immunosuppressive treatments as covariates will be applied.

OS and EFS probabilities will be estimated and displayed using the Kaplan Meier method.

The analysis of secondary time-to-event endpoints with competing risks (e.g. time to response, response duration, time to cGvHD development) will be performed by means of the Aalen Johanson estimator for the calculation of cumulative incidence rates. Appropriate Regression models (Cox models for OS, EFS, Fine and Gray models for endpoints with competing events) will be applied. For FFS, different types of failure will be analyzed separately, considering the other types of failure and onset of cGvHD as competing events. For evaluating QOL, scores will be calculated according to the EORTC QLQ-C30 Scoring Manual [24]. The scores at screening will be summarized and for different time points during follow-up, differences of the scores to the screening scores will be calculated in FAS and the PP set.

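### Duration of response is confined to responders yet falls under the planned Fine and Gray models; a treatment coefficient from that subset would not be a randomised comparison

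*Protocol article*

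**What the plan says.** Only the protocol article is at hand.

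- **Definition (Secondary endpoints).** The endpoint is "Duration of response, assessed for responders only by calculating the time from first response to the date of first observation" of acute GvHD relapse or progression, or to the date further immunosuppression is given. On competing events: "Onset of chronic GvHD (cGvHD) or death without prior observation of aGvHD relapse or progression is considered to be a competing events".
- **Analysis (Statistical planning).** "The analysis of secondary time-to-event endpoints with competing risks (e.g. time to response, response duration, time to cGvHD development") is to use cumulative incidence estimates. The next sentence adds: "Appropriate Regression models (Cox models for OS, EFS, Fine and Gray models for endpoints with competing events) will be applied".
- **What is not said.** No sentence calls duration of response descriptive or gives non-responders a duration of zero. No covariates are named for the time-to-event models. For the logistic models of the primary and binary secondary endpoints, treatment assignment is named.
- **Planning assumption (Statistical planning).** The trial is sized for the case "when the response probabilities are 50% (ruxolitinib) and 30% (BAT").
- **Durability endpoints that keep all randomised patients (Secondary endpoints).** One is the proportion in each arm with a response "persisting for at least 4 consecutive weeks within 8 weeks after randomization". Another is failure-free survival, measured from randomisation, which counts new systemic immunosuppression as a failure.

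**The concern.** A patient enters this analysis only by responding, and response is the outcome the treatment is meant to change. If ruxolitinib produces responses that BAT alone would not, the ruxolitinib responder group contains patients whose counterparts on BAT are excluded. Adjusting for GvHD grade and number of previous treatments does not restore the balance that randomisation gave to the whole arms.

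A treatment coefficient fitted in responders therefore mixes two things: any effect on how long a response lasts, and a difference in who responded. It could suggest shorter responses on ruxolitinib when no patient's response was shortened. It could also hide a real lengthening, or show one that is not there.

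**Working it through.** **1. The plan's own figure.** For 30% v 50%, one-sided α = 5%, power 80%, pooled χ² formula without continuity correction:

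n per arm = [1.645·√(2·0.4·0.6) + 0.842·√(0.3·0.7 + 0.5·0.5)]² / 0.2² = (1.140 + 0.571)² / 0.04 ≈ 73.1, rounded up to 74, so 148 in total.

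Then 148 × 1.08 = 159.8, so 160 randomised. Both stated figures reproduce. The article gives no figure for duration of response.

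**2. How different the responder groups are.** At 80 per arm, 80 × 0.30 = 24 responders on BAT and 80 × 0.50 = 40 on ruxolitinib plus BAT. At most 30% of patients can be responders on either arm. So at least (50 − 30)/50 = 40% of ruxolitinib responders, 16 of 40, have no counterpart among BAT responders. These rates are the day-28 assumptions; duration starts at first response, so the actual responder counts may differ.

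**3. Effect on a responder-only comparison.** Assumptions, none of them from the documents:
- 30% of patients respond on either arm, and a further 20% respond only with ruxolitinib.
- Durations are exponential, with a 26-week median in the first group and no drug effect on it.
- The added responders have median m weeks.
- There are no competing events.

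Proportion still in response at 26 weeks after onset:
- BAT responders: 2^(−26/26) = 50%.
- Ruxolitinib responders: 0.6 × 50% + 0.4 × 2^(−26/m).
- As a share of all randomised: BAT 0.30 × 50% = 15%; ruxolitinib 15% + 20% × 2^(−26/m).

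| Median m of added responders | Responders only, ruxolitinib v BAT | Simulated Cox hazard ratio, responders only | Simulated trials of 80 per arm with ratio above 1 | All randomised, ruxolitinib v BAT |
|---|---|---|---|---|
| 39 weeks | 55% v 50% | not run | not run | 28% v 15% |
| 26 weeks | 50% v 50% | 1.0 | 49% | 25% v 15% |
| 13 weeks | 40% v 50% | 1.3 | 81% | 20% v 15% |
| 8 weeks | 34% v 50% | 1.5 | 91% | 17% v 15% |

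The hazard ratios come from one large simulated sample per row, censored at 52 weeks. The trial shares come from 400 simulated trials per row.

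The last column favours ruxolitinib by construction, because added responders can only add to the total. It shows that the two comparisons can point in opposite directions, not what the trial will find.

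**4. With a real benefit.** Suppose the true hazard ratio is 0.7 in patients who respond on either arm. Their 26-week proportion on ruxolitinib is 0.5^0.7 = 61.6%.
- m = 13: 0.6 × 61.6% + 0.4 × 25% = 47%, against 50% on BAT.
- m = 8: 0.6 × 61.6% + 0.4 × 10.5% = 41%, against 50%.

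A real benefit is masked in both cases. A larger one can outweigh the selection: at a hazard ratio of 0.5 and m = 13, 0.6 × 70.7% + 0.4 × 25% = 52% against 50%.

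**The case against.** **No arm comparison is stated.** A reader might infer that the article expressly plans to compare duration of response between arms. It does not. Time to response carries a sentence on comparing treatment arms; duration of response carries none, and covariates for the time-to-event models are not listed. This stands as a limit on wording. But regression models are said to be applied to this class of endpoint, response duration is named in the class, and in a two-arm trial treatment is the obvious covariate.

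**The direction is unknown.** A reader might infer that ruxolitinib will look worse. Nothing in the documents says that added responses are shorter. With equal durability this source gives no bias, and with longer durability the bias favours ruxolitinib. This stands. The lack of comparability does not depend on direction.

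**The illustration is not the planned model.** It uses Cox regression without death or chronic GvHD competing, and the article's retrospective series reports 1-year survival of 62.4% in acute disease, so death is not negligible. It also counts time from response rather than from randomisation. The figures therefore show a mechanism and a plausible range. They do not forecast the Fine and Gray estimate.

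**Durability is partly covered.** Sustained response and failure-free survival already count everyone randomised, so readers would not depend on duration of response alone. This lessens the consequence. Neither gives the probability of being in response over time.

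**Hematologic relapse.** A reader might also see an error in its absence from this endpoint's competing events, since time to response and time to chronic GvHD include it. The documents do not support that. Relapse does not rule out a later GvHD flare or new immunosuppression, and follow-up continues after treatment ends. Observing patients through relapse is a legitimate choice.

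**Conclusion.** The point holds in a limited form. Duration of response is confined to a subset formed after randomisation and is placed among endpoints for which regression is planned, with nothing marking it as descriptive. If treatment is a covariate in that model, which is inferred, its coefficient is not a randomised effect.

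Under the stated assumptions the responder-only hazard ratio ranges from about 1.0 to 1.5 with no patient's response shortened, and the bias reverses if the added responses are the more durable ones. The size rests wholly on assumed durations; the non-comparability rests only on the plan's own 30% and 50%. This concerns one secondary endpoint. The primary response analysis and the sample size stand as they are.

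**What to change.** - State that duration of response in responders is reported descriptively by arm (cumulative incidence curves), without a between-arm regression or test.
- Base any arm comparison of durability on all randomised patients: the probability of being alive and in response over time since randomisation, through a fixed horizon, with non-responders contributing zero.
- State how crossover is handled in that analysis. One rule is to count BAT patients as not in response from the date they cross over to ruxolitinib. Another rule would serve if fixed in advance. Without one, responses obtained on ruxolitinib could be credited to the BAT arm.
- Present the result beside the existing sustained-response and failure-free survival endpoints.

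The cost is a change of analysis wording and one added analysis from data already collected. The downside is a less familiar summary than duration among responders.
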